### Exercise intervention and active control groups

#### Yoga arm

The yoga intervention consists of two weekly, 90-min group sessions for 12 weeks. The style of yoga selected for the intervention is Hatha yoga, the most popular form of yoga practice in the USA [28] which focuses on practicing physical poses, breathing, and meditation. STAY Fit yoga sessions will be held at a local yoga studio and taught by a certified yoga instructor, who has been instructing and practicing for more than 20 years. Each 90-min session is structured such that participants perform 60-min of stretching and poses (*asana*), 15 min of guided breathing practice (*pranayama*), and 15 min of guided meditation. Table 2 depicts a sample yoga session. Sessions are designed at a beginner level for the first few weeks, with a focus on helping participants develop good form, proper alignment, and postures for the asanas. Props used during the sessions include a yoga mat, chair, blanket, and blocks.

**Table 2 Tab2:** Sequence of Hatha yoga and stretching-toning exercises from week 1 of the STAY Fit Trial

Yoga	Stretching and toning
Poses (*asanas)*	Back arch
*Ardha Matsyendrasana*—twist in simple seated pose	Forward bend
*Marjaryasana/Bitilasana*—cat and cow	Squat
*Tadasana*—mountain pose	Military press
**Utkatasana*—chair pose	Walking dips
*Urdhva Hastasasana*—upward salute	Bicep + fly arm cycle
**Virabhadrasana*—warrior 1 and 2	Wood chop
**Purvottanasana*—intense side stretch	Tricep extension
*Viparita Karani*—Supported legs on the seat of a chair	One leg stand
*Supta Baddha Konasana*—reclining bound angle pose	Side leg abductions
*Supported Savasana*—corpse pose	Bicycle abdominal twist
Breathing (*pranayama*)	
3 parts breath in *Supta Baddha Konasana*	
Mediation	
Guided meditation/body scan while in supported *savasana*	

Note: *Using chair for support

#### Aerobic walking intervention arm

Participants randomized to the walking intervention arm will meet three times a week, 60 min a session, for the 12-week intervention. The intensity of each walking session will be individualized for each participant. The 12-week structure of the walking sessions, including the intensity and duration for each week’s sessions, is presented in Table 3. The rating of perceived exertion (RPE) and target heart rate (HR) zones were selected in accordance with the ACSM exercise prescription guidelines for cancer survivors. Within each 4-week block, participants started at the lowest recommend intensity for 15 min, gradually increasing the duration to 40 min with the target HR zone. Prior to the start of the intervention, researchers will calculate each participant’s target HR zones using the Kavonen formula [29] ([(HR_max_ − HR_rest_) × % training intensity] + HR_rest_), where HRmax = 220 − age and HRrest = resting heart rate recorded at baseline submaximal treadmill test. All walking sessions are led by trained exercise leaders, who are trained with the detailed protocol for the sessions, and complete 2-h-long orientations to review the manual of procedures and protocols including participant safety, leading warm up and cool down exercises and adapting the intensity of exercise to target the HR zones. During each session, exercise leaders are responsible for monitoring the participant’s heart rate every 5 min to ensure they stay within their designated heart rate zone. Participants will be allowed to freely change the speed and/or incline during the session to stay in the target HR zone. If needed, participants will be given wrist and/or ankle weights to wear to keep them at a higher intensity. Sessions will begin with a 5-min warm up including dynamic stretching and brief aerobic activity (e.g., marching in place, high knees) and end with a 5-min slow walking cool down and static stretching until the participant HR returns to pre-exercise resting levels.

**Table 3 Tab3:** ACSM’s aerobic exercise prescription for cancer survivors and protocol for the STAY Fit walking group

Weeks	1–4	5–8	9–12
Rating of perceived exertion	12–13	14–15	16–17
Target heart rate zone (% of heart rate reserve)	40–59	60–70	70–89
Duration (minutes)	15–40	15–40	15–40

#### Stretching and toning control arm

Participants randomized into the stretch and toning group will participate in sessions three times a week for 60 min each for the duration of the 12-week program. This group will participate in exercises that target all major muscle groups and work toward balance, toning, and flexibility. A sample stretching and toning exercise sequence is presented in Table 2. A given week will consist of the same exercises, but more reps and/or sets will be added over the course of the week’s sessions (Monday to Wednesday to Friday) building from 1 to 2 sets and 8 to 12 reps. Stretches and balance exercises were timed starting at 10 building up to 30 s. Exercises are designed to be progressive and challenging over the 12-week study period. At the beginning of each session, participants will walk around the perimeter of the room for 5 min and then engage in a 5-min warm up stretching routine. During the warm-up and before beginning the exercises, the leaders will inform the participants about the exercises, repetitions, and sets for the session. The exercise leaders will track the number of sets, repetitions, and time for exercises that are time-based (e.g., planks). Exercise leaders will provide posture and breathing cues throughout the session and demonstrate modifications for exercises when a participant presents mobility or functional limitations. The sessions will end with a 5-min cool down consisting of static stretching. Stretching and toning sessions will take place in an exercise studio and will be led by trained exercise leaders. Similar to the walking exercise leaders, these are given a manual detailing the protocol for the sessions and complete 2-h long orientation and training sessions to learn about participant safety, warm-up, stretching and toning exercises and modifications, and cool down stretches.

#### Exercise logs, attendance, and adherence

Prior to each session, participants in all groups will be fitted with a chest-strap heart rate monitor (Polar Model F1), which will record their heart rates over the session. At each session, participants will be given an exercise log, where they are to record their resting heart rate, average heart rate for the session, their self-reported rating of perceived exertion using the Borg scale [30], and self-reported enjoyment (a 1–5 Likert scale). The supervising exercise leader will keep track of the total minutes of exercise for the day and will review the logs for completeness before concluding the exercise session.

Attendance will be monitored by the respective exercise leaders for the 3 groups. A binder with attendance sheets for the 12 weeks will be presented to the exercise leaders at the first exercise session. Exercise leaders will be responsible for recording attendance and noting announced and unannounced absences. To promote adherence to the study protocols, participants will receive follow-up phone calls for any unannounced absences. They will also be given a mid-session feedback report (6 weeks, i.e., halfway into the intervention), providing averages of their weekly heart rates, rating of perceived exertion, enjoyment ratings, overall attendance percentage, and personalized feedback from their respective exercise leaders. Lastly, two times throughout the study period, exercise leaders will hold a raffle with prizes donated from local businesses (free fitness classes at a local gym) that can be redeemed after the trial ends.

In the event where a participant has decided to drop out of the study, their decision will be noted, and the participant will be contacted to administer follow-up assessments. Participants must have attended at least one session in order to be contacted for follow-up.

#### Home logs

Throughout the duration of the 12-week program, the participants will complete weekly home logs to track any participation in physical activity outside of the program. New home logs will be given to participants on Fridays and the completed home logs from the previous week will be collected by the exercise leaders on Mondays. Participants will be encouraged to record the type of physical activity they participated in, the intensity of the activity including an RPE rating and their enjoyment. If the participant does not engage in any home exercise, they will be asked to indicate “None” on the log.

### Adverse events and data safety monitoring

A data safety and monitoring plan has been established and approved by the University Institutional Review Board (IRB) that will allow us to consistently monitor and report adverse events to the University IRB. An official data safety and monitoring committee was not deemed necessary for this trial, as this is a single site, low-risk intervention. However, the investigators and research staff will meet on a weekly basis to review trial proceedings and participant status. All participants will be encouraged to report any health-related changes to the study staff. The exercise leaders will also closely monitor safety and follow up with participants in case of unannounced absences. If a participant discontinues exercise due to a health issue, the research staff will seek permission from their physician for resuming participating in the exercise program. If there is any recurrence of cancer or need for treatment (chemotherapy, radiation, or surgery) during the 12-week exercise sessions for a participant, he/she will be requested by the PI to discontinue participation in the trial as a safety and precautionary measure. Other than this, there will be no special criteria for discontinuing or modifying allocated interventions or stopping the trial.

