### Statistical analysis

Data will be analyzed using SPSS 24.0 (IBM Corp., Armonk, NY). Each of the cognitive domains assessed will be analyzed separately. From each of the assessments administered, latent variables will be created to represent a global cognitive score for each domain. These variables will be created for both baseline and post-intervention test scores. Given the pilot nature of this study, we will focus on descriptive statistics and calculating effect sizes (Cohen’s d values). Data characteristics permitting (normality, multi-collinearity, sample size), we may conduct additional secondary analyses. For example, a time (baseline, follow up) × group (yoga, aerobic, stretching-toning) repeated measures analyses of covariance controlling for relevant covariates (possible covariates include age, education, stage of cancer, months since diagnosis, attendance, and baseline performance) can be employed to explore intervention effects for each of the cognitive domains. Similar repeated measures analyses could examine intervention effects for cardiovascular fitness and the tertiary psychosocial outcomes. Given that this is a pilot study, no additional subgroup or adjusted analyses are planned. An intent-to-treat analysis approach will be used for any dropouts who completed at least one exercise session. Missing data will be handled using a mean imputation approach. Participants’ exercise session attendance and physical activity performed outside of the session (as reported in home logs) will be factored into analyses as appropriate to control for participants’ adherence to study protocols.

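### The recurrence rule takes participants out of the trial rather than only out of the exercise, and the text does not secure their 12-week cognitive tests and questionnaires.

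*Protocol article*

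**What the plan says.** All quotations are from the protocol article.

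- **Adverse events and data safety monitoring, recurrence rule.** If cancer recurs or treatment is needed during the exercise period, the participant "he/she will be requested by the PI to discontinue participation in the trial as a safety and precautionary measure".
- **Same section, the sentence before.** Other health problems are handled differently. The wording there is "If a participant discontinues exercise due to a health issue", and the person may resume with a physician's permission.
- **Same section, the sentence after.** "Other than this, there will be no special criteria for discontinuing or modifying allocated interventions or stopping the trial".
- **Exercise logs, attendance, and adherence.** The recall rule opens "In the event where a participant has decided to drop out of the study" and provides that "the participant will be contacted to administer follow-up assessments". Its one explicit condition is "Participants must have attended at least one session in order to be contacted for follow-up".
- **Statistical analysis.** "An intent-to-treat analysis approach will be used for any dropouts who completed at least one exercise session". Missing values are to be filled by mean imputation, and the stated emphasis is that "we will focus on descriptive statistics and calculating effect sizes".
- **Measures; Discussion.** Outcomes are taken at baseline and after 12 weeks, with no later visit.

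**The concern.** Stopping a treatment and leaving a trial are different events. An intent-to-treat analysis needs outcomes from people who stop treatment, and a rule that ends trial participation puts those outcomes at risk. Here the safety reason concerns exercising, but the rule as worded reaches everything, including tests done seated and questionnaires filled in at home.

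The participants affected are not a random subset. The Background ties loss of mental acuity to cancer and its treatment, so someone whose cancer returns, or who starts treatment, may well score worse at 12 weeks. Mean imputation would replace that score with an average one. Because the pilot concentrates on descriptive statistics and effect sizes, the 12-week arm means are a main output, and an affected arm would look slightly too good. The Background also says the pilot tests procedures for a larger trial, so the wording could be carried forward.

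**Working it through.** **1. The wording.** The health-issue sentence stops the exercise. The recurrence sentence stops participation in the trial. The sentence after it speaks of allocated interventions and of stopping the trial, so it does not settle which was meant. The recall rule is framed around a participant's own decision. No sentence says that people stopped at the investigator's request go unassessed, and none says that they are assessed.

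**2. Inputs.** The plan gives no figure for this point, so there is none to reproduce.
- From the document: 25 per arm, 75 in total (Sample size calculation); mean imputation (Statistical analysis).
- Assumed, because the document is silent: k = 0 to 3 participants lost per arm; each truly δ = 0.5 to 1 SD worse than the imputed value; the arm's own mean is imputed (the plan does not say which mean); recurrence or new treatment in p = 1% to 4% over 12 weeks, equal in all arms.

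**3. Shift in one arm's mean**, k × δ / 25:
- smallest with a loss: 1 × 0.5 / 25 = 0.02 SD
- largest: 3 × 1.0 / 25 = 0.12 SD

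**4. Shift in a two-arm contrast**, |k₁ − k₂| × δ / 25:

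| Losses in the two arms | Shift (SD) |
|---|---|
| equal | 0 |
| 1 v 0 | 0.02 to 0.04 |
| 3 v 1 | 0.04 to 0.08 |
| 3 v 0 | 0.06 to 0.12 |

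Simulation with δ = 1 (100,000 runs) gave 0.040 for 1 v 0, 0.080 for 3 v 1 and 0.120 for 3 v 0, matching the formula.

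**5. Scale.** The standard error of a two-arm difference is √(2/25) = 0.283 SD. A shift of 0.04 is 0.04/0.283 = 14% of it, and 0.12 is 0.12/0.283 = 42%.

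**6. Average effect with equal recurrence in each arm.** The mean shift of each arm is p × δ, from 0.01 × 0.5 = 0.005 to 0.04 × 1 = 0.04 SD. It is the same in every arm, so the expected contrast bias is 0. Simulation with δ = 1 (200,000 runs) gave an arm bias of 0.020 at p = 2% and 0.040 at p = 4%, with contrast bias 0.000 in both. At p = 2% the SD of the contrast was 0.285 with full data and 0.286 with imputation, so precision is essentially unchanged.

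**7. How often it would arise.**

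| p | Expected events in 75 | P(no events in 75) | P(gap of 3 or more between two given arms, either direction) |
|---|---|---|---|
| 1% | 0.75 | 47% | 0.3% |
| 2% | 1.5 | 22% | 1.7% |
| 4% | 3 | 5% | 6.9% |

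**The case against.** The strongest reply is that the plan already covers these people. The recall rule speaks of someone leaving the study and still calls that person back, so in this document leaving does not mean the end of assessment. The investigator only requests withdrawal, so a participant who agrees has arguably decided to leave. The one explicit condition on recall is an attended session, and the intent-to-treat sentence covers any dropout who meets it. The sentence after the recurrence rule mentions allocated interventions, which suggests that stopping the intervention was what the authors had in mind. Details of recall may also sit in the monitoring plan or the manual of procedures, neither of which is shown.

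This reading is plausible, and for that reason the point is only that assessment is not secured. It does not remove the literal rule. The article chose a wider term than in the sentence just before, and staff following it could skip the 12-week visit. This is a rule stated too broadly rather than a detail left out.

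A second reply is that one of the assessments is itself a treadmill test to 85% of predicted maximum heart rate, so caution may properly reach beyond the sessions. That stands for the treadmill test, but not for the cognitive tests or questionnaires.

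A third is that the effect is close to nil. That stands for the between-arm contrast. Mean imputation is also a separate weakness, which this change leaves in place; what the change does is reduce the number of values that need imputing.

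**Conclusion.** The concern holds, as a cheap improvement rather than a serious flaw. The recurrence rule is broader than its purpose, and the recall rule does not clearly make up for it.

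The gain lies in the arm-level results and in resting the intent-to-treat analysis on observed values. It does not lie in a less biased yoga contrast: nothing in the document suggests that recurrence would differ by arm, and any shift in a contrast would come from chance imbalance. Events should be few, since participants are at least a year past their last treatment, have none planned, and are followed for 12 weeks. With no events there is no effect. All the sizes rest on assumed recurrence rates, an assumed cognitive deficit and own-arm imputation, and they would shrink further if some of those invited declined.

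**What to change.** - In Adverse events and data safety monitoring, reword the recurrence sentence so that the investigator asks the participant to stop the exercise intervention, not the trial.
- In Exercise logs, attendance, and adherence, extend the follow-up contact to participants stopped at the investigator's request.
- Invite those who are willing to the 12-week cognitive tests and questionnaires. Leave the treadmill test to clinical judgement.
- Analyse them in their assigned arm, and report the numbers and reasons for stopping by arm.

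The safety decision is unchanged. The cost is one reworded sentence, a few added words, and up to two optional laboratory visits for a few ill participants, some of whom will decline. Full visits run to about 2 h each, but the timed tests in Table 1 take less: 5 + 8 + 15 + 5 + 10 = 43 min in the first session, and 4 + 15 = 19 min plus one self-paced task in the second. The questionnaires are completed at home, so someone too ill to travel could still give quality-of-life data.

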### Subjects

The inclusion criteria are low physical activity engagement (i.e., less than 150 min of moderate to vigorous exercise per week), including no yoga practice over the last 6 months; aged between 30 and 70 years; capable of performing yoga, aerobic walking, or stretching and toning exercise without any pre-existing condition(s), as determined by their personal physician; the type of cancer (i.e., types of brain cancers are excluded as they could confound with cognitive study outcomes); the last treatment for cancer being at least 1 year from the beginning of the exercise program; not planning to receive any cancer-related treatment during the study period; intention to stay in the Champaign-Urbana area over the duration of the study; comfortable with reading, writing, and speaking English; and willingness to be randomized. Finally, all participants will be required to complete the Physical Activity Readiness Questionnaire (PAR-Q [17];) and must obtain approval from their personal physician, if deemed high-risk on the PAR-Q. The physician approval process will be facilitated by the research staff to minimize participant burden.

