#### Cardiovascular function (secondary outcome)

The secondary outcome of the trial is cardiovascular function. A submaximal treadmill test will be administered at baseline and after the 12-week intervention. We will use a modified Balke protocol [26] that estimates a participant’s predicted VO2max based on the incline, speed, and heart rate over the last two stages completed during the test. The modified Balke is a well-accepted treadmill protocol that keeps the speed constant (3.0 mph) and workload by increasing the incline by 2.5% every 3 min. The test will terminate when the participant reaches 85% of their age-predicted maximum heart rate. We will then use their speed, incline, and heart rate from the last two completed stages, as well as their age-predicted maximum heart rate, to calculate their predicted VO2_max_ [27]. Before the test, anthropometric measurements including height, weight, resting heart rate, and resting blood pressure will be recorded. During the test, blood pressure and a rating of perceived exertion [26] will be recorded every 3 min for participant safety. Test will conclude once participant’s reach their 85% predicted maximum heart rate. In the event of participants taking prescription medications that are beta-blockers, a rating of perceived exertion of 17 will serve as an indicator for test termination. All participants will be led into a 3-min walking cool down at 2.0 mph followed by a 2-min seated rest. Heart rate and blood pressure will be monitored throughout the cool down to ensure participant is back at his/her resting state.

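### Walking-arm heart-rate zones rest on 220 minus age with no exception for beta-blocker users, whom the protocol anticipates in the treadmill test, and no rule says whether RPE or heart rate governs

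*Protocol article*

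**What the plan says.** **Walking arm** (Protocol article, Aerobic walking intervention arm). Before the programme starts, "researchers will calculate each participant’s target HR zones using the Kavonen formula", with HRmax taken as 220 − age and HRrest as the resting rate measured at the baseline treadmill visit. Leaders check "heart rate every 5 min to ensure they stay within their designated heart rate zone". Walkers may change speed and incline to stay in the zone. The section adds: "If needed, participants will be given wrist and/or ankle weights to wear to keep them at a higher intensity". Table 3 gives, for weeks 1–4, 5–8 and 9–12, zones of 40–59%, 60–70% and 70–89% of heart rate reserve beside RPE bands of 12–13, 14–15 and 16–17. The section does not mention beta-blockers.

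**Treadmill test** (Cardiovascular function). The test normally ends at 85% of age-predicted maximum heart rate. For "participants taking prescription medications that are beta-blockers, a rating of perceived exertion of 17 will serve as an indicator for test termination". Predicted VO2max is still computed from heart rate and age-predicted maximum, with no exception for these participants.

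**Other relevant text.** Beta-blocker use is not an exclusion (Subjects). Participants must be able to do the exercise in the judgement of their own physician, and they "must obtain approval from their personal physician, if deemed high-risk on the PAR-Q". At each session they log a "self-reported rating of perceived exertion using the Borg scale" (Exercise logs, attendance, and adherence). The section on adverse events and data safety monitoring describes close safety monitoring by leaders, weekly staff review of participant status, physician permission to resume after a health issue, and discontinuation for cancer recurrence or treatment. It then ends: "Other than this, there will be no special criteria for discontinuing or modifying allocated interventions or stopping the trial".

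**The concern.** The protocol expects some participants to be on beta-blockers and accepts that an age-predicted heart rate is a poor stopping point for them in a supervised test done twice. The walking arm applies the same age-predicted maximum to everyone for up to 36 sessions (3 per week × 12 weeks), and the leader actions it describes follow heart rate.

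A walker whose heart rate is held down by medication will read as below the zone. The stated response to a low reading is more speed, more incline or added weights. If RPE is already at or above the Table 3 band, the two columns of the table point in opposite directions, and the article does not say which one the leader should follow.

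Two things are at stake for this subgroup of one arm. One is safety, since the walker may be overexerted. The other is fidelity, since the aerobic dose delivered may differ from the dose prescribed.

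**Working it through.** The plan gives no figure on this point to reproduce. The check applies its own zone formula and re-expresses the result against a lower true peak.

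**Inputs from the protocol**
- Zone limit = (HRmax − HRrest) × % + HRrest, with HRmax = 220 − age.
- Percentages from Table 3: 40–59, 60–70, 70–89.
- Age range 30 to 70; 25 participants per arm.

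**Assumptions (not in the documents)**
- Resting rate 60 bpm, the same in the formula and in the true reserve.
- True peak 10% or 20% below 220 − age.
- Beta-blocker use in 5%, 10% or 20% of participants.

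**Step 1. Zones at age 60.** HRmax = 160 and reserve = 160 − 60 = 100. The zones are 100–119, 120–130 and 130–149 bpm.

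**Step 2. The same zones as a share of true reserve**, (zone limit − 60) / (true peak − 60):

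| Weeks | Intended | Peak 144 (10% lower, reserve 84) | Peak 128 (20% lower, reserve 68) |
|---|---|---|---|
| 1–4 | 40–59% | 48–70% | 59–87% |
| 5–8 | 60–70% | 71–83% | 88–103% |
| 9–12 | 70–89% | 83–106% | 103–131% |

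For example, 89/84 = 106% and 70/68 = 103%.

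**Step 3. When the weeks 9–12 zone becomes unreachable**
- Top of zone above true peak: blunting greater than 1 − 149/160 = 6.9%.
- Whole zone above true peak: blunting greater than 1 − 130/160 = 18.8%.
- Age 50 (zone 137.0–157.9, HRmax 170): 7.1% and 19.4%.
- Age 70 (zone 123.0–140.1, HRmax 150): 6.6% and 18.0%.

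**Step 4. Does the measured resting rate correct this?** The weeks 9–12 limits can be written as 0.70 × HRmax + 0.30 × HRrest and 0.89 × HRmax + 0.11 × HRrest. A resting rate 10 bpm lower moves them by only 3.0 and 1.1 bpm. The 220 − age term dominates.

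**Step 5. Sensitivity to the assumptions.** At age 60 with resting rate 65 and peak lowered by 10, 20 or 30 bpm, the weeks 9–12 zone becomes 78–99%, 89–113% or 102–130% of true reserve. Across the ages checked (30 to 70) and resting rates of 55 and 65, a 20 bpm reduction puts the top of that zone at 104–116%. A 10 bpm reduction puts it at 96–101%, which is at the edge.

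**Step 6. How many walkers.** Expected users among 25 are 25p = 1.25, 2.5 or 5 for p = 0.05, 0.10 or 0.20. The chance of at least one is 1 − (1 − p)^25 = 72%, 93% or 99.6%. These figures only restate the assumed prevalence.

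**The case against.** Five points can be made in defence of the plan.

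1. **The article may simply be silent.** Leaders are trained on a manual of procedures that is not shown and could hold a medication rule. This stands as a caution. However, the article does more than omit a rule: it states one, for every participant, that works badly for a group it names elsewhere.

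2. **Table 3 prescribes RPE as well as heart rate.** A walker above the RPE band is already outside the prescription, so overexertion is an inference and not an instruction. This stands in part. No sentence puts heart rate above RPE, but none puts RPE above heart rate either, and the monitoring and adjustment described are tied to the zone.

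3. **There are safeguards.** Physician judgement and PAR-Q clearance, self-chosen speed and incline, leader safety monitoring, weekly staff review and the week-6 feedback report (which shows heart rate and RPE before weeks 9–12) all reduce the risk. None of them is an intensity rule.

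4. **The adverse-events section does not forbid tailoring.** A reader might infer from "Other than this, there will be no special criteria for discontinuing or modifying allocated interventions or stopping the trial" that intensity may not be adapted for beta-blocker users. The documents do not support that. The sentence closes a paragraph on safety and withdrawal, while the walking and stretching sections both describe adapting exercise to the individual.

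5. **The contrast with the treadmill test is narrower than it looks.** A reader might infer that the protocol abandons age-predicted heart rate for these participants there. It does so only as the stopping indicator. A stopping rule and a training prescription also serve different purposes. The contrast still shows that the limitation was recognised in one place and not in the other.

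**Conclusion.** The point holds in limited form. The walking-arm section fixes zones from 220 − age for all walkers and does not say that RPE governs when the two measures conflict, although beta-blocker users are anticipated in the treadmill test. Under the worked assumptions, modest blunting (about 7% at ages 50 to 70) puts the top of the weeks 9–12 zone out of reach, and about 18–19% puts the whole zone out of reach.

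The size rests on an assumed resting rate and assumed blunting. The number of users is not given and is probably small; there may be none in the arm. The documents do not show that any walker would be harmed. Nor do they describe a zone-compliance record in which such a walker would be counted as out of zone: the logs hold resting and average heart rate, RPE and enjoyment, and the leader tracks minutes. No stopping rule or monitoring committee is missing on this account. This is an optional, cheap improvement.

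**What to change.** Add to the Aerobic walking intervention arm section:

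> For participants taking beta-blockers, the Table 3 RPE band governs intensity in place of the heart-rate zone; speed, incline or weights are not increased to reach the heart-rate zone once RPE is within the band.

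No change to the adverse-events section is needed.

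**Cost.** One sentence in the protocol, a line in leader orientation and an IRB notification. RPE is already prescribed and logged, and beta-blocker use must already be known for the treadmill test, so no new data, equipment or visits are required. The downside is that intensity for these few walkers (about 1 to 5 of 25 under the assumed prevalences) is self-rated and so less objective.

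The planned study period ended in May 2020, before the article appeared. The practical value therefore lies mainly in the larger trial that this pilot is meant to inform.
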